# The effectiveness and safety of *Kami Guibi-tang* for mild cognitive impairment: study protocol of a pilot, randomized, placebo-controlled, double-blind trial

**DOI:** 10.1186/s13063-019-3567-1

**Published:** 2019-07-22

**Keywords:** Mild cognitive impairment (MCI), *Kami Guibi-tang*, Herbal medicine, Seoul Neuropsychological Screening Battery (SNSB), Magnetic Resonance Imaging (MRI), Brain metabolite, Brain neurotransmitter, Cerebral blood flow (CBF)

## Abstract

**Background:**

Mild cognitive impairment (MCI) is an intermediate phase between normal aging and dementia. Since a majority of amnestic MCI (aMCI) cases progress to Alzheimer’s disease (AD), it is considered the prodromal stage of AD and, therefore, a treatment target for the prevention of further cognitive decline. However, there is no approved treatment for MCI at present. *Kami Guibi-tang* (KGT) is a herbal drug used in Korean medicine to treat amnesia, insomnia, loss of appetite, and depression. We will explore the effectiveness and safety of KGT in amnestic MCI in this trial.

**Methods/design:**

The study will be a single-center, randomized, placebo-controlled, double-blind trial. Eligible participants diagnosed with amnestic MCI will be randomly allocated to a treatment or control group. Participants will take KGT or placebo granules, three times a day, for 24 weeks. The primary outcomes will be changes in Seoul Neuropsychological Screening Battery (SNSB) scores, and magnetic resonance imaging (MRI) measurements including those of brain metabolites, neurotransmitters, and cerebral blood flow. The secondary outcomes will include the safety assessment, measured by changes in blood chemistry, changes in blood protein and cholesterol levels related to AD pathology, and a comparison of MRI changes between the two groups, using age and genotype as covariates.

**Discussion:**

This study will be the first clinical trial to identify the therapeutic potential of *Kami Guibi-tang* for amnestic MCI. The findings will provide insight into the feasibility of large-scale trials to gather evidence for KGT as a treatment for MCI.

**Trial registration:**

Korean Clinical Trial Registry, ID: KCT0002407. Registered on 30 March 2017.

**Electronic supplementary material:**

The online version of this article (10.1186/s13063-019-3567-1) contains supplementary material, which is available to authorized users.

## Background

Mild cognitive impairment (MCI) is an intermediate phase between normal aging and dementia. This clinical condition is characterized by self or caregiver-reported memory or cognitive complaints, and objective cognitive impairment, that is not severe enough to interfere with daily activities [1]. The majority of people with MCI develop dementia due to Alzheimer’s disease (AD) [2]. In particular, the amnestic subtype of MCI, which manifests as memory complaints, is often caused by degenerative etiologies and is generally regarded as a precursor of AD. A previous study revealed that 16% of amnestic MCI (aMCI) patients progress to dementia each year, 99% of whom receive an AD diagnosis [3]. Early treatment of mild-to-moderate AD is associated with better responses than later treatment, so treatment of MCI may delay progression to AD [4]. There is, however, no treatment approved for enhancing *memory function, or preventing further cognitive decline in MCI* [5]*.*

*Kami Guibi-tang* (KGT) is a popular herbal medicine used in Korean and Kampo medicine to treat amnesia, insomnia, loss of appetite, and depression. Several studies have explored the effects of KGT on cognitive impairment, particularly in AD. KGT improved learning performance in a mouse model of accelerated senescence [6], and reduced spatial memory impairment induced by scopolamine or delta-tetrahydrocannabinol [7]. In the 5XFAD mouse model of AD, KGT improved deficits in object recognition memory, and reversed the degeneration of cortical axons and presynaptic terminals [8]. A clinical study demonstrated that the Mini-Mental State Examination (MMSE) score of AD patients improved after receiving orally administered KGT extract granules for 3 months [9].

Previous studies have suggested that KGT could be beneficial for cognitive function in AD patients. However, few clinical trials have been published, and no study has yet investigated the effect of KGT on MCI. This pilot study aims to determine the effectiveness and safety of KGT for improving cognitive function, the influence on neuroimaging and neurochemical biomarkers, and the potential therapeutic effects in MCI.

## Methods/design

### Study design and setting

This study will use a single-center, randomized, double-blind, placebo-controlled, parallel-group clinical trial design. The study will take place at Kyung Hee University Hospital at Gangdong, Seoul, Korea from March 2017 through November 2019. The flow chart of the study design is shown in Fig. 1. The schedules for enrollment, interventions, and assessments are shown in Table 1.

**Fig. 1 Fig1:**
[figure not shown]
Flow chart of the study design

**Table 1 Tab1:**
[figure not shown]
The schedule of enrollment, interventions, and assessments (SPIRIT 2013 Statement)

### Participants

#### Inclusion criteria

Participants who meet all of the following criteria will be eligible to participate:Aged 55–90 years, with complaint of impaired memoryObjective cognitive impairment as measured by the Seoul Neuropsychological Screening Battery (SNSB), with a score of 3 on the Global Deterioration Scale (GDS), 0.5 on the Clinical Dementia Rating (CDR), and a normal score on the Korean MMSE (K-MMSE)Diagnosed with aMCI by a neurologistParticipants who have not taken medication affecting cognitive function, including gliatilin, gliatamine, ginexin, tanamin, or other psychoactive drugs, in the previous 2 weeksParticipants who have not changed medication for underlying diseases in the previous 2 weeks, and no expected change in medication during the study periodNo difficulty in communicating

#### Exclusion criteria

Participants who meet any of the following criteria will be ineligible to participate:Diagnosed with AD, based on the criteria of National Institute of Neurological and Communicative Disorders and Stroke and Alzheimer’s Disease and Related Disorders Association (NINCDS-ADRDA)Brain disorders causing neurological symptoms, other than cognitive impairmentParkinson’s disease, Huntington’s disease, Down’s syndrome, Creutzfeldt-Jakob disease, or any other neurodegenerative disorderCognitive impairment resulting from other diseases including head trauma, hypoxic brain damage, vitamin deficiency, brain tumor, encephalitis, neurosyphilis, and mental retardationCerebrovascular diseases with magnetic resonance imaging (MRI) evidenceA previous or current history of major depressionConcomitant psychiatric disorders or behavioral problems that require antipsychotic medicationA history of a convulsive disorder, except for febrile convulsion during childhoodUnstable or life-threatening medical conditionsUncontrolled hypertensionHeart or renal diseasesPeripheral edemaGastrointestinal symptoms such as anorexia, nausea, abdominal pain, or diarrheaTaking medication that could induce hypokalemia or myopathyDrug hypersensitivity to the constituents of the study medicationPossibility of pregnancyClinically significant abnormalities in blood chemistry test results, including levels of serum aspartate aminotransferase/alanine aminotransferase (AST/ALT) more than two-fold the upper normal limit, or serum creatinine (Cr) level more than 10% of the upper normal limitParticipation in any other clinical trials within the previous 4 weeksIlliteracyContraindications for MRIConsidered unsuitable for participation by the investigators

#### Drop-out criteria

Occurrence of any severe adverse effectsParticipants’ voluntary withdrawal from the trialParticipants not following the protocol (i.e., drug compliance below 80%)Use of additional medication to improve cognitive function during the study periodDecision made by the principal investigator

### Recruitment, enrollment

We will recruit a total of 38 patients through advertisements and referrals and screen the candidates aged 55–90 years, with complaints of impaired memory, using the inclusion/exclusion criteria, the K-MMSE, and the Korean Dementia Screening Questionnaire (KDSQ). Potentially eligible participants will undergo the SNSB, and those who are diagnosed with aMCI by a neurologist will be included in the trial. The investigators will provide a detailed explanation of the purpose, procedures, and potential risks and benefits of the study. Participants willing to participate in the trial and provide biological specimens will sign a consent form prior to enrollment.

### Randomization, allocation, blinding

A researcher uninvolved in the assessment will generate a random sequence using SPSS ver. 18. We will randomly allocate participants to either the treatment or the control group, in a 1:1 ratio using the block randomization method, with a block size of 4. The participants, assessor, clinical trial pharmacist, and researchers will be blinded to the allocations throughout the course of the study. Cases will be unblinded only if serious adverse events (SAE) occur.

### Intervention

After randomization, the treatment group will receive KGT granules (3 g/pack) and the control group will receive placebo granules (3 g/pack). *Kami Guibi-tang*, the herbal medicine under study, is composed of 14 drugs: *Astragali Radix* (1.0 g), *Ginseng Radix* (1.0 g), *Atractylodis Rhizoma* (1.0 g), *Poria cocos* (1.0 g), *Zizyphi Fructus* (0.67 g), *Zingiberis Rhizoma* (0.33 g), *Saussureae Radix* (0.33 g), *Glycyrrhizae Radix* (0.33 g), *Zizyphi Spinosi Semen* (1.0 g), *Longan Arillus* (1.0 g), *Angelicae Radix* (0.67 g), *Polygalae Radix* (0.67 g), *Bupleuri Radix* (1.0 g), *Moutan Radicis Cortex* (0.67 g), and *Gardeniae Fructus* (0.67 g). Treatment granules will be manufactured by Kyoung Bang Pharmaceutical Co., Ltd. (Incheon, Korea), which has been certified for Good Manufacturing Practice.

Placebo granules will be produced by the same manufacturer, using the standard method of placebo manufacturing according to the Korean Good Manufacturing Practice guidelines. The placebo will be similar to the *Kami Guibi-tang* granules in appearance, taste, and smell.

An independent clinical pharmacist will distribute KGT or placebo granules to the study participants. The pharmacist will instruct participants to dissolve the granules in hot water, stir well, and drink the solution three times per day, 30 min after meals, for 24 consecutive weeks. The researchers will call participants by phone once a week, reminding them to comply with the medication schedule.

The administration of medicine for underlying diseases, such as hypertension or diabetes mellitus, will be permitted during the intervention; however, any medication that can affect cognitive function will be prohibited. We will ask the participants to report all medications taken during the study at each visit, and record the names, duration, and dosage of the drugs on the case report form (CRF).

Participants will be required to return the unused trial drugs at the next visit. The number of returned drugs will be assessed to evaluate drug compliance, and participants with less than 80% compliance will be excluded.

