### Assessments

#### K-MMSE and SNSB

The K-MMSE will be performed at the screening visit and after 12 weeks of medication, to screen for MCI and assess the cognitive status of participants. This is a simple screening test for the longitudinal assessment of general cognition [10].

The full version of the SNSB-II will be measured at baseline and after 24 weeks of medication, to evaluate the effect of *Kami Guibi-tang* on cognitive function. The change in the mean of the SNSB scores, including the SNSB for dementia (SNSB-D) scores, will be compared between the KGT and placebo groups as a primary outcome.

The SNSB is one of the standardized neuropsychological test batteries, widely used in South Korea, for assessing general cognitive abilities. The test is composed of multiple subtests, which evaluate five cognitive aspects: attention, memory, language, visuospatial function, and executive function. Other related tests are included, such as the K-MMSE, Clinical Dementia Rating (CDR), Barthel–Activities of Daily Living (BADL), and Geriatric Depression Scale (GDS). The estimated completion time of the whole battery is 1.5–2 h [11].

A modified version of the original SNSB for dementia (SNSB-D) will be used to provide a general cognitive functioning (GCF) score, drawn from the sum of five domains. The maximum total score is 300 points consisting of 17/300 (6%) for attention, 27/300 (9%) for language and related function, 36/300 (12%) for visuospatial function, 150/300 (50%) for memory, and 70/300 (23%) for frontal/executive function [12]. The contents of the SNSB-D are shown in Table 2.

**Table 2 Tab2:** Contents of the Seoul Neuropsychological Battery for Dementia (SNSB-D)

Domains (total score)	Subtests	Maximum points
Attention (17)	Digit span forward	9
	Digit span backward	8
Language and related function (27)	K-BNT	15
	Calculation	12
Visuospatial function (36)	RCFT copy	36
Memory (150)	Orientation	6
	SVLT free/delayed recall	48
	SVLT recognition	12
	RCFT free/delayed recall	72
	RCFT recognition	12
Frontal/executive function (70)	Motor impersistence	3
	Contrasting program	3
	Go-no-go test	3
	Fist-edge-palm	3
	Luria loop	3
	Categoric word generation	20
	Phonemic word generation	15
	Stroop test-color reading	20
GCF score		300

*K-BNT* Korean short version of the Boston Naming Test, *RCFT* Rey Complex Figure Test, *SVLT* Seoul Verbal Learning Test, *GCF* global cognitive function

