#### MRI

Participants will undergo brain MRI at baseline and after 24 weeks of medication, to measure changes in brain metabolite and neurotransmitter levels, cerebral blood flow, tissue volume, and to evaluate brain abnormalities.

Proton magnetic resonance spectroscopy (^1^H-MRS) will be used to measure brain metabolite and neurotransmitter levels. Single-voxel Point-RESolved Spectroscopy (PRESS) MRS will be performed at the precuneus and posterior cingulate area of the brain, with a voxel size of 30 mm × 30 mm × 30 mm, to detect *N*-acetylaspartate (NAA) and glutamate-glutamine complex (Glx, with both Glu and Gln). *N*-acetylaspartate and Glx will be quantified using LCModel software. MEshcher-GArwood (MEGA) PRESS MRS will be performed to detect gamma-aminobutyric acid (GABA) in the same area as the PRESS MRS. The amount of GABA will be quantified using GANNET software. Pseudo-continuous arterial spin-labeling (pCASL) MRI will be performed to measure cerebral blood flow (CBF) in the brain. Voxel-based CBF will be mapped using local software. A three-dimensional T1-weighted image will be acquired using the magnetization-prepared rapid gradient-echo (MPRAGE) sequence, to quantify the gray and white matter tissue volume in the brain. T2-weighted turbo-spin echo (TSE), and fluid attenuation inversion recovery (FLAIR) sequences, will be used to evaluate brain abnormalities in participants. Changes in CBF and mean levels of NAA/Cr, Glx/Cr, and GABA/Cr, will be compared between KGT and placebo groups, as a primary outcome.

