### Statistics

#### Sample size calculation

This clinical trial is a pilot study to examine the feasibility of a full randomized clinical trial of KGT, and to determine the sample magnitude required for large-scale studies. To our knowledge, no prior study has investigated the effect of KGT on MCI. There are no previous data indicating the sample size needed to yield statistically significant results for determining the effect of KGT by the SNSB scores. For pilot trials, the sample size of 10–20 participants per group was suggested by Kieser and Wassmer. [13]. Browne recommended using at least 30 subjects to estimate parameters [14]. Our target sample size is 30, so 38 individuals will be recruited to allow for a 20% dropout rate.

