#### Data analyses

The investigators, along with an independent professional statistician, will perform the data analyses. All statistical analyses will be performed using SPSS for Windows. The effectiveness test will be performed using the intention-to-treat (ITT) principle and the per-protocol (PP) principle. Missing data will be adjusted with the last-observation-carried-forward (LOCF) imputation method. The safety test will be analyzed using the ITT principle, without adjustment. We will not perform interim analysis.

The student’s *t* test will be used for parametric variable comparisons between the two groups, and the paired *t* test will be used for intra-group comparisons. The Mann-Whitney *U* test will be used for non-parametric variable comparisons between the two groups, and the Wilcoxon signed-rank test will be used for intra-group comparisons.

The paired *t* test will be used to compare changes in MRI measurements, blood proteins, and cholesterol levels, before and after treatment. Correlation analysis will be used to estimate the relationship between the changes in MRI measures and changes in blood test results. Linear regression analysis will be used to compare changes in MRI measures, between the study group and the placebo group, using age and *APOE* genotype as covariates. Statistical significance will be set at *P* < 0.05, and all tests will be two-tailed.

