### Adverse events

An undesirable, unexpected sign, symptom, or disease that occurs during the trial will be identified as an adverse event (AE), regardless of any causal relationship with the study intervention. Adverse events will be checked for at every visit, from assessment of participants’ subjective reports and by objective examination, including blood tests and ECGs. Monitoring will also be performed by phone each week during the intervention period, and 4 weeks after the end of treatment. All AEs will be recorded in the CRF by the site investigator and assessed for severity and causality. Details of each AE will be recorded, including start and end date, feature, duration, severity, and causal relationship to the study medication.

Serious adverse events (SAEs) are defined as illness requiring hospitalization, events that result in persistent or significant disability or incapacity, events deemed life-threatening, death, a congenital anomaly or birth defect, or other important medical conditions. If SAEs occur, study participation will be discontinued, appropriate measures will be taken immediately, and the Institutional Review Board (IRB) will be notified as soon as possible. All occurrences of AEs will be monitored until they subside or stabilize.

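### The unqualified exclusion of participants below 80% compliance, taken literally, is incompatible with the planned ITT analysis, and its scope needs to be fixed

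*Protocol article*

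**What the plan says.** All references are to the protocol article.

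- **Intervention.** Unused drug is returned at the next visit and counted, and "participants with less than 80% compliance will be excluded". The sentence names no analysis set.
- **Drop-out criteria.** Compliance below 80% and use of additional cognitive medication stand in one list with severe adverse effects, voluntary withdrawal from the trial and a decision of the principal investigator.
- **Adverse events.** "If SAEs occur, study participation will be discontinued". The wording concerns participation, not study drug alone.
- **Data analyses.** "The effectiveness test will be performed using the intention-to-treat (ITT) principle and the per-protocol (PP) principle". Neither is named as primary. "Missing data will be adjusted with the last-observation-carried-forward (LOCF) imputation method". For safety: "The safety test will be analyzed using the ITT principle, without adjustment".
- **K-MMSE and SNSB; MRI.** The primary outcomes have two time points: "The full version of the SNSB-II will be measured at baseline and after 24 weeks of medication", and "Participants will undergo brain MRI at baseline and after 24 weeks of medication". Under Blood testing, the blood biomarkers (secondary) have the same two.
- **Sample size calculation.** "Our target sample size is 30, so 38 individuals will be recruited to allow for a 20% dropout rate".

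**The concern.** Compliance is known only from returned drug, so exclusion on it happens after randomisation. The same is true of starting a cognitive drug or having a serious adverse event. These events may reflect tolerability or decline, and both can differ between KGT and placebo. An ITT analysis exists to keep such people in the comparison. A rule that excludes them, with no statement of what they are excluded from, leaves three readings open: they stop treatment, they stop being assessed, or they are left out of the PP set only. Only the first and third leave ITT intact.

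The stake is larger than wording because of the visit schedule. With no SNSB or MRI between baseline and week 24, a participant whose assessments stop early has no post-baseline value to carry forward. No later analysis can recover a week-24 assessment that was not made. The pilot is also meant to supply the figures for sizing a larger trial, so a distorted between-group estimate would be passed on.

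**Working it through.** **1. The plan's own figure.** Inputs from Sample size calculation: target 30, dropout 20%. 30 / (1 − 0.20) = 37.5, rounded up to 38. This reproduces. The plan therefore allows for 38 − 30 = 8 losses, 8/38 = 21% of those randomised. This allowance covers dropout for any reason, including voluntary withdrawal, so it is only a ceiling on the number affected by these rules.

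**2. The three readings.**

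- *Exclusion from the PP set only.* ITT is intact; the sentence in Intervention is too broad.
- *Exclusion from all effectiveness analyses.* The result is not ITT. See step 3.
- *Exit from follow-up, with LOCF.* ITT keeps the people but has no real endpoint for them. See step 4.

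**3. If excluded people leave the analysis.** Assumptions, not figures from the article: compliance and outcome change are bivariate normal with correlation r of 0.1 to 0.5, and the least compliant fraction q of each arm is removed. The mean change among those retained shifts by r × t(q), in SD, where t(q) = φ(z_q) / (1 − q).

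- t(0.30) = 0.497 and t(0.10) = 0.195; difference 0.302.
- 30% v 10% excluded: r = 0.1 gives 0.03 SD; r = 0.3 gives 0.09 SD; r = 0.5 gives 0.15 SD.
- 20% v 20% with the same r in both arms: 0 SD.

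The bias thus comes from a rate, or a link to outcome, that differs by arm. Exclusion as such does not produce it.

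**4. If they exit follow-up and LOCF is applied.** The only earlier SNSB or MRI value is baseline, so the change is set to 0. The week-12 K-MMSE cannot stand in for the SNSB or the MRI. With dropout p_T and p_C unrelated to outcome and mean changes m_T and m_C, the estimated difference is (1 − p_T) m_T − (1 − p_C) m_C.

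- p_T = p_C = 0.20: 0.80 × (m_T − m_C). A true difference shrinks to 80% of its value.
- p_T = 0.30, p_C = 0.10, no treatment effect, common change 0.3 SD: 0.21 − 0.27 = −0.06 SD. With common change 0.5 SD: 0.35 − 0.45 = −0.10 SD. A spurious difference appears.

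The split of 30% v 10% and the common change of 0.3 to 0.5 SD are assumptions. The article gives no expected rate by arm or by reason.

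**5. Scale.** With 15 per arm, the standard error of a difference in means is √(2/15) = 0.37 SD. The largest illustrated bias, 0.15 SD, is about 0.4 of one standard error.

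**The case against.** The strongest reply is that the plan already holds the answer. It announces a PP analysis beside ITT, and 80% compliance is a usual PP criterion. It also announces LOCF, which is needed only if people without week-24 data remain in the analysis. No sentence removes non-compliers from ITT, and detailed set definitions may sit in a full protocol or SAP not shown. This stands in part: a reader might infer a flat contradiction, and the article does not show one. The missing set definitions are not the fault here. The fault is the stated exclusion, which is broader than a PP rule and is repeated as a drop-out criterion beside withdrawal from the trial.

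A reader might also infer that week-24 outcomes are never collected from these people. That is not stated. Only Adverse events says that participation stops, and only for serious events. If compliance is judged over the whole course, it is known at week 24, when the outcomes are due anyway; the article does not say whether it is judged per visit or cumulatively. So the consequence in step 4 is conditional.

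A further tempting inference is that the pilot loses its adherence data. This is not supported: packs are counted before anyone is excluded, and a case report form is kept for each participant.

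Finally, a matched placebo, blinding and weekly calls to all participants make a large imbalance between arms less likely, though not impossible.

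**Conclusion.** The point holds in a limited form. Followed as written, exclusion below 80% compliance and the related drop-out and discontinuation rules are incompatible with the ITT effectiveness analysis, and the article leaves their scope open. If drop-out ends assessment, ITT becomes completers plus changes imputed as zero.

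The size is unknown. Under the stated assumptions it runs from about 0, when rate and mechanism are the same in both arms, to 0.03–0.15 SD if excluded people leave the analysis at 30% v 10%. Under baseline carried forward, a true difference shrinks to about 80% of its value with 20% dropped per arm, unrelated to outcome. It would be wrong to read the 20% allowance as a forecast that 8 of 38 will be lost through these rules, or to attach one specific bias figure to the trial. Neither has a basis in the article. The case for acting now is that unmeasured week-24 outcomes cannot be restored by analysis and that the remedy is cheap.

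**What to change.** Reconcile Intervention, Drop-out criteria, Data analyses and Adverse events so that they say the following:

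1. The ITT set is all randomised participants in their assigned arm, and it is the primary set for effectiveness.
2. The 80% compliance rule and use of prohibited medication define only the supportive PP set.
3. Week-24 SNSB, MRI and blood tests are sought from every randomised participant who has not withdrawn consent and can be assessed, whatever their compliance or study-drug status. Adverse events should state how the end of participation after a serious event relates to this.

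Whether study medication continues is a clinical decision and is not addressed here.

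The cost is a short amendment and a few already scheduled week-24 assessments in people off study drug. The benefit of item 3 is limited by timing: Trial status reports 33 participants enrolled of the 38 planned, so it helps only the remaining 5 and those of the 33 who have not yet reached week 24. Items 1 and 2 apply to all data already collected.
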